#### 8.1.16 cART resumption visit (7-10 days after first Qual pVL positive)

pVL-pos+7d visit will be performed at BCN-Checkpoint.

Following procedures will be performed:

- Reporting of symptoms suggestive of acute retroviral syndrome (including its severity grade)
- Discussion on treatment resumption based on following considerations (attachment M):
  - o If viral load is >2,000 copies/mL in visits pVL-pos and pVL-pos+3d, and/or clinical symptoms, laboratory abnormalities or significant drops in CD4 T cell counts (>50% &/or <500) have been detected, patients will be recommended to re-start cART immediately.
  - o If viral load is <2,000 copies/mL in visits pVL-pos and >2,000 copies/mL in visit pVL-pos+3d, and/or clinical symptoms, laboratory abnormalities or

significant drops in CD4 T cell counts (>50% &/or <500) have been detected, patients will be recommended to re-start cART immediately.

- If viral load is > or <2,000 copies/mL in visits pVL-pos and <2,000 copies/mL in visit pVL-pos+3d, and NO clinical symptoms, laboratory abnormalities or significant drops in CD4 T cell counts have been detected cART will not be resumed.
- cART prescription\* at the Pharmacy Unit
- Follow-up explanation and cART+4w visit scheduling (or a follow-up MAP visit at BCN-Checkpoint if cART is not resumed)
- CRF data collection

\*cART regimen will at the discretion of the study physician, according to clinical criteria (no changes on patient's previous cART regimen are envisioned as no emergence of drug resistances is expected)

Overall, time since 1st positive HIV-1 Qualitative detection to cART resumption is aimed to be <10 days to avoid fast viral reservoir replenishment.

[figure not shown]

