### **Role of Treatment Interruption in the current HIV cure research agenda:**

At the moment no reliable method has been validated to assess the predictive value of any in vitro test or parameter, one that could be benchmarked against a clinically relevant outcome for functional cure. Once a research strategy has proven safe and encouraging, allowing participants to interrupt their antiretroviral treatment remain the most reliable measure of viral persistence and will always be the final endpoint of strategies aimed at the cure of HIV infection. In 2014, at the HIV Cure IAS Symposium, Analytical Treatment Interruptions (ATI) which allowed a viral set point to be achieved after a usually fixed period of 16 weeks were recommended to be substituted for Monitored Antiretroviral Pause (MAP) strategies. MAP strategies are considered safer to study participants. During a MAP cART is restarted when viral rebound is detected which could hamper potential fast viral reservoir replenishment. In such cases, the efficacy of the strategy is measured as the time to viral rebound in the context of interventions aimed at reducing the HIV reservoir.

To adapt the trial design according to our patient characteristics and thanks to excellent collaboration with BCN-checkpoint community center in Barcelona with dedicated clinical staff and novel laboratory technology already in place, weekly close monitoring during the MAP phase will be performed to allow rapid detection of viral rebound and ensure fast treatment resumption in case of needed.

Lastly, and to minimize risks of the intervention, an early interim and futility analyses is planned for each individual before the MAP phase. Treatment interruption would be discouraged individually if boosting MVA.HIVconsv was shown to be no longer immunogenic after romidepsin administration ((no net increase in induced response compared to pre-vaccination levels with MVA.HIVconsv at BCN02-Romi baseline visit, due to RMD toxicity on CTL functional activity for instance) as an improved viral control would not be foreseen. In such situation, trial results would be focused on the viral reservoir and immunogenicity endpoints only until better correlates of control would be available to predict clinically relevant outcomes on which one could recommend treatment interruptions in a safer manner.

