  - 2.5. *In vivo* CTL toxicity assessment based on the most relevant marker from Endpoint 1 (viability, activation, ex) before RMD infusion and after 24 and 72h (RMD1), 12 and 72h (RMD2) and 12, 72 and 7 days (RMD3)
  - 2.6. Development of a population PK/PD analysis to integrate pharmacokinetics of RMD and *in vivo* observed effects of RMD
3. To evaluate the immunogenicity of booster vaccinations with MVA.HIVconsv before and after RMD administration and the effect on viral rebound control after discontinuation of cART.
    - 3.1. To evaluate immunogenicity of booster vaccinations, HIVconsv-specific T cell responses will be measured before, 1, 4 and 8 weeks after both booster vaccinations (MVA1 and MVA2) by IFN $\gamma$  ELISPOT using peptide pools covering different HIV proteins and HIVcons sequences. Total HIVconsv magnitude as well as HIVconsv focus over the rest of HIV-1 specific responses will be compared over time. These results will enable the futility analyses (see section 5.6)
    - 3.2. Evaluation of the effect MVA.HIVconsv boost vaccinations on viral suppressive capacity of CD8+ T cells in vitro, using a flow cytometric assay 4 weeks after MVA2.
    - 3.3. Determine the proportion of individuals who initiate a MAP following the futility analysis
    - 3.4. Determine the proportion of individuals who maintain sustained pVL <2,000 copies/ml during the first 12weeks after treatment cessation.
    - 3.5. Determine the proportion of individuals in whom cART is reinitiated due to viral rebound (2 consecutive pVL >2,000 copies/ml 3-5 days apart), >50% drop in CD4 cell counts, <450 cells/mm^3 and/or symptomatic acute retroviral syndrome.
    - 3.6. Evaluate the emergence of viral resistance during MAP phase
    - 3.7. Evaluate the viral suppression rates 6 months after treatment resumption.

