  - Plasma and PBMC storage following scheme detailed in attachment K
  - Discussion on treatment resumption once results from Biochemistry, Hematological parameters and CD4 cell count are available (72h): recommendation on cART resumption will be assessed based on clinical visit, willingness of patients to resume treatment, detection of viral load in the qualitative test and/or drop in CD4 cell counts.

After the first 12 weeks post-MAP (from W30):

- Fortnightly visits will be performed, including:
  - Qualitative viral load test (Xpert HIV-1 Qual de Cepheid)
  - Clinical visit, adverse event register
  - Reporting of symptoms suggestive of acute retroviral syndrome (including its severity grade)
  - Discussion on treatment resumption: recommendation on cART resumption will be assessed based on clinical visit, willingness of patients to resume treatment and detection of viral load in the qualitative test.
- Monthly:
  - Biochemistry and hematological parameters, viral load and CD4 count (performed at an external Lab)
  - Plasma and PBMC storage following scheme detailed in attachment K
  - Discussion on treatment resumption once results from Biochemistry, Hematological parameters and CD4 cell count are available (72h): recommendation on cART resumption will be assessed based on clinical visit, willingness of patients to resume treatment, detection of viral load in the qualitative test and/or drop in CD4 cell counts.

|                                                                                                           | Phase 2 (to be performed at BCN-Checkpoint) |    |    |    |    |    |    |    |    |    |    |    |                                                                |    |    |    |    |    |    |    |    |    |    |    |    |    |    |    |    |    |    |    |    |    |  |  |  |
|-----------------------------------------------------------------------------------------------------------|---------------------------------------------|----|----|----|----|----|----|----|----|----|----|----|----------------------------------------------------------------|----|----|----|----|----|----|----|----|----|----|----|----|----|----|----|----|----|----|----|----|----|--|--|--|

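### The CD4 limit for restarting cART is 500 in Protocol 8.1.16 but 450 in endpoint 3.5, so some CD4-only restarts that the protocol recommends meet no reason counted in 3.5

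*Protocol*

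**What the plan says.** Section 8.1.16 sets out when cART is to be restarted after a positive qualitative viral load test. Its first two considerations rest on viral load and/or clinical symptoms, laboratory abnormalities or CD4. Each gives the CD4 part in the same form: "significant drops in CD4 T cell counts (>50% &/or <500) have been detected, patients will be recommended to re-start cART immediately". The third consideration covers participants whose viral load is below 2,000 copies/ml at the visit three days later. They stay off treatment only if there are no other signals: "and NO clinical symptoms, laboratory abnormalities or significant drops in CD4 T cell counts have been detected cART will not be resumed".

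Endpoint 3.5 in section 5.3.2 is a proportion defined by reasons for restarting. It opens with "Determine the proportion of individuals in whom cART is reinitiated due to viral rebound (2 consecutive pVL >2,000 copies/ml 3-5 days apart" and continues with the CD4 reason, ">50% drop in CD4 cell counts, <450 cells/mm"³. It closes, after an and/or, with symptomatic acute retroviral syndrome.

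Section 8.1.15, on the scheduled visits during the pause, gives no CD4 number. Among the grounds for discussing resumption it lists "detection of viral load in the qualitative test and/or drop in CD4 cell counts". Attachment M, the decision chart that 8.1.16 cites, is not reproduced in the public document.

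**The concern.** One clinical decision has two absolute CD4 limits in current text, and no visible section reconciles them. The operating rule acts below 500; the endpoint that reports restarts by reason recognises an absolute count only below 450.

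The difference matters only where CD4 alone decides, and the third consideration of 8.1.16 shows that this can happen. Such a participant is advised to restart, yet 3.5 applied as written would not count the restart. At stake is whether 3.5 fully reports the restarts that the protocol's own rule produces.

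**Working it through.** **Inputs**
- Restart rule (8.1.16): CD4 fall above 50%, and/or CD4 below 500.
- CD4 reason counted (5.3.2, endpoint 3.5): fall above 50%, then a comma, then below 450 cells/mm³.
- Entry CD4 of at least 500 cells/mm³ (7.1).
- At most 24 participants (10.3).
- Assumption: the fall is measured from the count before the pause, B. The sections quoted do not name the reference value.

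**Rules for a CD4 count c**
- Restart recommended: c < 500 or c < B/2.
- Counted in 3.5, CD4 terms read as alternatives: c < 450 or c < B/2.
- Recommended but not counted: 450 ≤ c ≤ 499 and c ≥ B/2.

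**Whole-number counts in the gap**

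| Pre-pause CD4 (B) | B/2 | Counts missed by 3.5 | Number |
|---|---|---|---|
| 500 to 900 | 250 to 450 | 450–499 | 50 |
| 950 | 475 | 475–499 | 25 |
| 998 | 499 | 499 | 1 |
| 999 and above | 499.5 and above | none | 0 |

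From 999 upward, any count below 500 is already a fall of more than 50%, which 3.5 counts.

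**Worked case.** Let B = 600 and c = 470. The fall is (600 − 470)/600 = 21.7%. Viral load is below 2,000 at the three-day visit, with no symptoms or laboratory abnormality. Under 8.1.16, 470 < 500, so restart is recommended. Under 3.5 there are not two consecutive values above 2,000, the fall is not above 50%, the count is not below 450, and there is no retroviral syndrome. No reason is met.

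**Effect on the proportion.** One uncounted restart lowers 3.5 by 100/n points, where n is the number starting the pause (assumed to be the denominator). At the maximum, 100/24 = 4.2 points. For smaller, assumed numbers: 100/15 = 6.7 and 100/10 = 10.0.

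**After alignment.** With 3.5 set to a fall above 50% and/or a count below 500, its CD4 reason equals the restart rule and the gap is empty for every B.

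**Other restart reasons in 8.1.16 that 3.5 lacks.** Laboratory abnormalities are not listed in 3.5. Nor is the viral load pattern in the second consideration, "If viral load is <2,000 copies/mL in visits pVL-pos and >2,000 copies/mL in visit pVL-pos+3d": 3.5 asks for two consecutive values above 2,000, and this pattern has only one. That is a separate mismatch, about viral load and not CD4.

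**The case against.** The strongest reply is that little depends on this. Endpoint 3.5 is a descriptive secondary proportion with no test or threshold. A case also needs several conditions together: a positive qualitative test, a viral load below 2,000 three days later, no symptoms or laboratory abnormality, a CD4 count in a 50-cell range, a fall of 50% or less, and a participant who follows a recommendation. All of this stands, and it is why the point is minor. It does not make the two limits agree. Attachment M cannot do so either: whichever limit it holds, at least one of the two sections disagrees with it.

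Three stronger readings are tempting, and the protocol does not support them.
- **A much wider gap.** Only a comma separates the two CD4 terms in 3.5, so a reader might take them as jointly required. At B = 600 the missed range would then be 300–499, or 200 counts. But the list closes with and/or, and its ordinary reading makes each item an alternative, as in 8.1.16.
- **An inconsistency with endpoint 3.7.** That endpoint is to "Evaluate the viral suppression rates 6 months after treatment resumption". A reader might infer that the restarts counted in 3.5 must equal the resumptions followed in 3.7. Nothing requires this. Section 8.1.15 lets the participant's own wish to resume weigh in the decision, and such a restart enters 3.7 without meeting a reason in 3.5.
- **Harm to safety or to the efficacy signal.** The stricter limit is the one in the operating rule. Endpoint 3.4 and the 20% efficacy threshold in 10.1 are defined by viral load and do not use CD4.

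**Conclusion.** The concern holds as a minor inconsistency. The absolute CD4 limit is 500 in 8.1.16 and 450 in 3.5, so a CD4-only restart at 450–499 with a fall of 50% or less can be recommended by the protocol and yet meet no reason in 3.5.

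The gap is at most 50 cells/mm³, narrows above a pre-pause CD4 of 900 and is gone from 999. This rests on reading the CD4 terms of 3.5 as alternatives and measuring the fall from the pre-pause count. Each case would cost the proportion at least 4.2 points. That is the effect of one hypothetical participant, not an expected error: the protocol gives no CD4 distribution, so the number affected cannot be stated and may be zero.

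**What to change.** In 5.3.2, change the CD4 reason in endpoint 3.5 to: *CD4 fall of more than 50% and/or CD4 count below 500 cells/mm³*. Leave 8.1.16 as it is. Lowering it to 450 would also remove the mismatch, but it would loosen a protective limit in a design chosen because "MAP strategies are considered safer to study participants".

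So that 3.5 counts every restart that 8.1.16 recommends, add two separately listed reasons: laboratory abnormalities, and viral load above 2,000 copies/ml only at the three-day visit. Keep viral rebound defined by two consecutive values; the single-value restart should stand as its own reason and not be merged into it.

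Check that attachment M uses the limit of 500.

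The cost is a rewording of one endpoint and a check of one attachment. Visits, samples and the restart rule do not change, so no participant would restart later or less often than now.

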## 7 SELECTION AND WITHDRAWAL OF SUBJECTS

### 7.1 INCLUSION CRITERIA

1. Subject included in ChAd-MVA.HIVconsv\_BCN01 study with complete follow-up and included in BCN01-RO extension study.
2. Willing and able to give written informed consent for participation in the study
3. Willing and able to keep a good adherence to their cART regimen for the duration of the intervention phase.
4. Optimal virological suppression for at least 3 years defined as maintained pVL below limit of detection (based on current available assays, 20 or 40 copies/ml) allowing for isolated blips (<200 cop/ml, non-consecutive, >10% total determinations).
5. Being on a non-boosted integrase-inhibitor based regimen (raltegravir or dolutegravir) for at least 4 weeks at screening visit.
6. No new AIDS-defining diagnosis or progression of HIV-related disease.
7. Haematological and biochemical laboratory parameters as follows:
  - a. Haemoglobin > 10g/dl
  - b. Platelets > 100.000/dl
  - c. ALT ≤ 2.5 x ULN
  - d. Creatinine ≤ 1.3 x ULN
8. Serology: negative for hepatitis B surface antigen; negative for hepatitis C antibodies OR confirmed clearance of HCV infection (spontaneous or following treatment).
9. Available for follow up for duration of study (baseline + at the most 54 weeks) and willing to comply with the protocol requirements
10. Age ≥18 years
11. CD4 T cell count ≥500 cells/mm^3

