| Efficacy Endpoint                                                                                         |                                             | x  |    |    |    |    |    |    |    |    |    | x  |                                                                |    |    |    |    |    |    |    |    |    |    |    |    |    |    |    |    |    |    |    |    |    |  |  |  |
| # to be shipped to HGTP for processing in the same day (for virological and immunological studies)        |                                             |    |    |    |    |    |    |    |    |    |    |    |                                                                |    |    |    |    |    |    |    |    |    |    |    |    |    |    |    |    |    |    |    |    |    |  |  |  |
| ~ to be shipped to General Lab : results available at Checkpoint (Report by phone to the patients at 72h) |                                             |    |    |    |    |    |    |    |    |    |    |    |                                                                |    |    |    |    |    |    |    |    |    |    |    |    |    |    |    |    |    |    |    |    |    |  |  |  |

If qualitative pVL test is found positive (indicative of pVL >200 copies/ml), following procedures will be performed:

- Blood extraction including:
  - o Viral load, hematological parameters and CD4 count
  - o Plasma and PBMC storage following scheme detailed in attachment K
  - o pVL-pos+3d visit scheduling

pVL-pos+3d visit will be performed at BCN-Checkpoint and will include:

- Clinical visit, adverse event collection
- Reporting of symptoms suggestive of acute retroviral syndrome (including its severity grade)
- Blood extraction including:
  - o Viral load and CD4 count
  - o Genotype resistance test
  - o Plasma and PBMC storage following scheme detailed in attachment K
- cART resumption visit scheduling (pVL-pos + 7 days) at BCN-Checkpoint

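### Endpoint 3.5 and the restart rule in Section 8.1.16 set different limits for the same viral-load and CD4 reasons, so some protocol-directed restarts fall outside the endpoint

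*Protocol*

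**What the plan says.** Endpoint 3.5 (Section 5.3.2) is the proportion of participants in whom "cART is reinitiated due to viral rebound (2 consecutive pVL >2,000 copies/ml 3-5 days apart", or for a CD4 reason given as ">50% drop in CD4 cell counts, <450 cells/mm", and/or for symptomatic acute retroviral syndrome.

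Section 8.1.15 sets the path into the restart decision: "If qualitative pVL test is found positive (indicative of pVL >200 copies/ml), following procedures will be performed". Those procedures include a quantitative viral load on the day (visit pVL-pos) and another at visit pVL-pos+3d.

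Section 8.1.16 then gives three branches:
- Both values above 2,000: restart.
- "If viral load is <2,000 copies/mL in visits pVL-pos and >2,000 copies/mL in visit pVL-pos+3d": restart as well.
- Second value below 2,000, whatever the first, with no symptoms, laboratory abnormalities or CD4 fall: no restart.

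In the two restart branches clinical findings are joined by and/or, so viral load alone is enough. On CD4 the text reads "significant drops in CD4 T cell counts (>50% &/or <500) have been detected, patients will be recommended to re-start cART immediately".

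Endpoint 3.4 in the same list is "Determine the proportion of individuals who maintain sustained pVL <2,000 copies/ml during the first 12weeks after treatment cessation". Section 7.1 allows entry with "CD4 T cell count ≥500". Section 10.3 caps enrolment at 24.

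**The concern.** Endpoint 3.5 classifies restarts by cause, and Section 8.1.16 is the rule that produces those restarts. Both put numbers on viral load and on CD4, and the numbers differ. The 3-5 day spacing in 3.5 fits the pVL-pos and pVL-pos+3d pair, so the two texts appear to describe the same two draws.

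Read literally, 3.5 leaves out participants whom the protocol restarts because of viral load or a CD4 fall. Whoever computes 3.5 must either apply the written definition and drop them, or count them and depart from it. With at most 24 participants, each such choice visibly moves the reported proportion.

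**Working it through.** **1. Viral load.** The four possible patterns, with no other trigger:

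| pVL-pos | pVL-pos+3d | Section 8.1.16 | Rebound reason in 3.5 |
|---|---|---|---|
| >2,000 | >2,000 | restart | met |
| <2,000 | >2,000 | restart | not met |
| >2,000 | <2,000 | no restart | not met |
| <2,000 | <2,000 | no restart | not met |

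Only the second row conflicts. A further value above 2,000 at the day-7 visit would be 7 - 3 = 4 days after the second draw and would satisfy 3.5. However, the procedures listed for that visit in 8.1.16 include no viral load, and the advice is to restart at once.

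**2. CD4, no fall above 50%.**
- 450-499: restart advised by 8.1.16; CD4 reason in 3.5 not met.
- Below 450: restart advised; 3.5 met if 450 is a separate limit.

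The comma in 3.5 leaves that last point open. If a drop above 50% and a count below 450 are both required, the gap widens: a fall from 600 to 440 is 160/600 = 26.7%, which meets 8.1.16 but not 3.5.

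Size of fall that lands in 450-499:
- From 500 (the entry floor): 500 - 499 = 1 to 500 - 450 = 50 cells, or 0.2% to 10%.
- From 600: 101 to 150 cells, or 16.8% to 25%.

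**3. Effect per person.** 1/24 = 4.2 percentage points, and more if fewer pause. If 12 paused (an assumed number), 1/12 = 8.3 points.

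**4. How often the conflicting viral-load row could occur.** This needs assumptions, because the protocol gives no growth rate:
- steady log-linear rise of g log10 per day;
- test positive from 200 copies/ml (Section 8.1.15);
- tests every 7 days, with participants not restarted retested 7 days later;
- second draw exactly 3 days after the first;
- no earlier symptom, laboratory or CD4 trigger.

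From 200 to 2,000 is 1 log10, which takes 1/g days. Let t be the days from crossing 200 to a test. The first value is below 2,000 if t < 1/g, and the second is above it if t + 3 > 1/g. The conflicting row therefore needs 1/g - 3 < t < 1/g with t positive, a window of min(3, 1/g) days. With test times uniform over the 7-day cycle:

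share of viral-load restarts = min(3, 1/g) / 7

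| g (assumed) | 1/g (days) | Window (days) | Share |
|---|---|---|---|
| 0.10 | 10 | 3 | 42.9% |
| 0.20 | 5 | 3 | 42.9% |
| 0.33 | 3.03 | 3 | 42.9% |
| 0.40 | 2.5 | 2.5 | 35.7% |
| 0.50 | 2 | 2 | 28.6% |

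With the fortnightly visits after week 12 of the pause, the divisor is 14: 3/14 = 21.4% down to 2/14 = 14.3%.

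Steps 1 to 3 do not depend on g.

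**The case against.** A restart rule may properly act earlier than an endpoint definition. Section 8.1.16 aims for restart within 10 days of the first positive test to limit reservoir replenishment, which explains not waiting for a third draw. Two values above 2,000 is also the protocol's standard for virological failure on treatment (Sections 7.3.1 and 7.3.2). This defends the restart rule, and it would cover a trigger such as laboratory abnormalities, which 3.5 does not list. It does not explain why an endpoint that counts restarts by cause uses different numbers for the same two causes. No visible text says the difference is intended.

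The attachments with the visit schedule and the decision chart (J and M) and the flowchart are not reproduced, and restart is advice after discussion. These limits stand. The body text of 8.1.16 is nonetheless explicit.

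Several stronger readings are not supported:
- **Any single value above 2,000 leads to restart.** Only the +3d value acts. A first value above 2,000 followed by one below it does not.
- **Endpoint 3.5 counts nothing beyond two viral loads or CD4 below 450.** It also lists a CD4 drop above 50% and acute retroviral syndrome. A participant with either is not lost.
- **Endpoints 3.4 and 3.5 contradict each other.** They are not complements. 3.4 concerns viral load over 12 weeks; 3.5 concerns restarts, has no time limit and includes other causes.
- **About 7 to 10 of 24 would be misclassified.** That multiplies the modelled share by 24 (24 x 0.286 = 6.9; 24 x 0.429 = 10.3). It requires all 24 to pause and all to restart on viral load, whereas Sections 7.3.4 and 10.2 provide for discouraging the pause in some.

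**Conclusion.** The definition is wrong as written, but the point is minor. Two groups restarted under the protocol's own rule do not meet 3.5 when no other trigger is present: those with a value below 2,000 then one above it, and those with CD4 450-499 without a 50% drop. Confidence is medium because of the attachments that are not shown.

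The firm size is at least 4.2 percentage points per affected participant. The 29-43% share of viral-load restarts is illustrative only and holds under the listed assumptions with weekly testing.

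A reader might infer that efficacy or safety conclusions are at risk; the documents do not support that. The >20% signal in Section 10.1 rests on viral load below 2,000 at week 12 of the pause, not on 3.5. The restart rule is the more cautious of the two texts. Endpoint 3.5 is one descriptive secondary endpoint with no test or threshold attached.

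**What to change.** Leave Section 8.1.16 unchanged and reword endpoint 3.5:

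- **Viral-load reason:** restart on pVL above 2,000 copies/ml at pVL-pos+3d, whatever the pVL-pos value, or on the confirming value when restart is decided at a scheduled quantitative visit. Show restarts with two consecutive values above 2,000 as a subset.
- **CD4 reason:** a drop above 50% or a count below 500, with the word or stated. Show counts below 450 as a subset.
- **Other reasons** (for example laboratory abnormalities or participant choice): tabulate separately, outside the proportion for rebound, CD4 fall and acute retroviral syndrome, so that 3.5 stays cause-specific.

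The cost is a wording change, with no new visit, sample or delay to restart. The downside is some loss of specificity: one value above 2,000 can count as the rebound reason, and a participant who enters at 500 needs to lose only 1 cell to fall below the CD4 limit. The stricter subsets keep that visible. Keeping 450 in 3.5 and tabulating all restarts by reason would also be defensible, but the endpoint would then need to say that it is deliberately narrower than the restart rule.
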